### Confidentiality

The aspects of confidentiality are as follows:

Participant confidentiality: Assign unique identifiers to participants to anonymize data while maintaining linkage to individual records internally. Implement strict access controls to restrict data access to authorized personnel only. Define user roles and permissions based on the principle of least privilege to limit access to specific data sets.Data encryption: Apply encryption protocols to protect stored and transmitted data. Encrypt sensitive information to prevent unauthorized access in case of a security breach.Confidentiality agreements: All personnel involved in the study must sign confidentiality agreements. Emphasize the importance of respecting participant privacy and the confidential nature of study data. Store physical and electronic data in secure environments. Implement measures such as locked cabinets for physical documents and secure servers for electronic data.

### Plans for Collection, Laboratory Evaluation, and Storage of Biological Specimens for Genetic or Molecular Analysis in This Trial/Future Use

There will be no collection, laboratory evaluation, or storage of biological specimens.

### Statistical Methods

#### Statistical Methods for Primary and Secondary Outcomes

The demographic and baseline characteristics and follow-up outcomes will be described as mean, SD, median, and range for continuous variables, and percentage for categorical variables. Descriptive statistics will be calculated for the whole sample and by relevant subgroups (age, gender, diagnosis, etc). Statistically significant differences across groups will be detected using 1-way ANOVA. Multiple linear regression will be performed to investigate the impact of participant characteristics on short- and medium-term outcomes.

This study will use the official Italian EQ-5D-5L questionnaire to measure health and quality of life. The EQ-5D-5L descriptive system includes 5 dimensions: mobility (MO), self-care (SC), usual activities (UA), pain/discomfort (PD), and anxiety/depression (AD). Each dimension is articulated into 5 severity levels: no problems, slight problems, moderate problems, severe problems, and extreme problems (or unable to). Consequently, 3125 (55) possible health states are determined by response combinations and identified with a unique 5-digit number ranging from perfect health (“11111”) to the worst state (“55555”). Each health state will be converted into a single index value from 0 (assigned to death) to 1 (perfect health state), using predefined preference weights collected at the population level.

All statistical analyses will be performed using R software (R Project for Statistical Computing).

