### Objectives

#### Primary Objectives

The project involves a web-based registry developed to facilitate data collection and evaluation of several different surgical, oncological, and socioeconomic outcomes of lung cancer patients diagnosed in early and locally advanced stages in Italy.

The primary objective is to generate data relevant to performance assessment through the development of national performance benchmarks based on the analysis of risk-adjusted outcomes and the processes of care indicators (eg, How does individual center X compare to the national standard in terms of length of stay for a certain subgroup of patients?).

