### Interventions

#### Explanation for the Choice of Comparators

The choice of comparators in this study is driven by the need to assess and compare various surgical interventions for lung cancer patients. The study aims to enroll patients eligible for minimally invasive manual, robot-assisted, or traditional open surgery, reflecting the diverse landscape of surgical approaches in clinical practice.

The rationale for including these comparators is rooted in the evolving nature of lung cancer treatment, where different surgical modalities are employed based on factors such as tumor characteristics, patient condition, and advancements in surgical techniques. Minimally invasive surgeries, including robot-assisted procedures, have gained prominence for their potential benefits, such as reduced postoperative pain, shorter hospital stay, and quicker recovery compared to traditional open surgery.

By including these comparators, this study seeks to evaluate and compare the outcomes of these diverse surgical interventions. This comprehensive approach allows for a nuanced understanding of the effectiveness and potential differences in results associated with each surgical modality. It also enables the study to contribute valuable insights into the evolving landscape of lung cancer treatment, guiding future clinical decisions and optimizing patient care.

The choice of comparators aligns with the study’s overarching objective to generate data for performance assessment. This provides a basis for national benchmarks and facilitates a thorough analysis of outcomes and care processes. This approach ensures that the study captures the diversity of surgical practices in the real-world setting, reflecting the dynamic nature of lung cancer treatment and contributing to the broader knowledge base in the field.

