#### Intervention Description

The interventions in this study encompass a spectrum of surgical approaches for lung cancer patients diagnosed in the early and locally advanced stages.

Regarding the rationale for intervention selection, the choice of interventions reflects the diversity of surgical practices in treating lung cancer. Each intervention has its advantages and considerations, and the study aims to evaluate and compare their outcomes comprehensively. Including minimally invasive and robot-assisted surgeries acknowledges the evolving landscape of surgical techniques, aligning with the contemporary emphasis on reducing patient morbidity and improving recovery.

Patients meeting the inclusion criteria will be assessed for eligibility, and the choice of intervention will be based on factors such as tumor characteristics, patient condition, and the surgeon’s expertise.

Qualified and experienced health care professionals will perform the surgical procedures at participating institutions. Data related to the interventions, perioperative details, and postoperative outcomes will be systematically collected through the web-based registry developed for the study.

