### Sample Size

LUCENT adopts a nonspecific sample size approach, allowing for the inclusion of eligible participants based on the defined criteria. The study aims to enroll a diverse and representative sample of lung cancer patients diagnosed in early and locally advanced stages to capture a comprehensive range of outcomes and experiences. Participants meeting the inclusion criteria will be recruited consecutively from participating institutions to ensure a systematic and unbiased selection process. The study will involve multiple centers across Italy to enhance the diversity and generalizability of the study findings. Data collection will be facilitated through a web-based registry developed for the study, allowing for standardized and centralized data collection from various participating sites.

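### The named test for group differences, 1-way ANOVA, pools one variance across groups whose sizes and spreads this nonrandomized design does not control; Welch's form would hold its 5% level at almost no cost

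*Protocol article*

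**What the plan says.** The statistical methods section for primary and secondary outcomes names two inferential tools. For comparing groups, "Statistically significant differences across groups will be detected using 1-way ANOVA". For covariates, "Multiple linear regression will be performed to investigate the impact of participant characteristics on short- and medium-term outcomes". No unequal-variance form, robust standard error, transformation or rank test is mentioned.

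The ANOVA sentence does not define its groups or list its outcomes. The sentence before it reads "Descriptive statistics will be calculated for the whole sample and by relevant subgroups (age, gender, diagnosis, etc", so demographic and diagnostic subgroups are the nearest candidates. Surgical approach is another, since the section on the choice of comparators states "The study aims to enroll patients eligible for minimally invasive manual, robot-assisted, or traditional open surgery" and says that their outcomes will be compared.

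On how groups arise, Intervention Description says that "the choice of intervention will be based on factors such as tumor characteristics, patient condition, and the surgeon’s expertise". The allocation section confirms that the study is nonrandomized. On size, "LUCENT adopts a nonspecific sample size approach", with consecutive recruitment. The continuous outcomes named elsewhere include length of stay (the example under Primary Objectives), costs (Additional Outcomes and Considerations; Table 1) and the EQ-5D-5L index.

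**The concern.** The question is whether group means differ. The reference distribution of the pooled-variance F test represents a narrower null: equal means and equal variances. The difference is harmless when groups are similar in size, or similar in spread. When both differ, the pooled error term mainly reflects the largest group, while the between-group term gives the smaller groups' variances more weight.

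Two errors follow. If a smaller group is the more variable, the test rejects equal means too often. If the largest group is the more variable, the test becomes conservative and misses real differences. The direction depends on case mix, which this study lets vary. A larger registry does not cure it, because the distortion depends on the proportions and the SD ratios, not on the total. Linear regression with ordinary constant-variance standard errors would share the weakness.

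The point is narrow. It would remain for a continuous outcome with independent patients and no confounding.

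**Working it through.** **Inputs from the article.** Test: 1-way ANOVA. Three surgical approaches. No sample size, group shares, SDs or alpha are given, so there is no figure of the plan's own to reproduce.

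**Assumed.** Nominal 5% level; three groups; splits of 45/35/20, 60/25/15 and 70/20/10 percent; one group's SD 1.25 to 2 times that of the others; equal true means unless stated.

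**Step 1: why the test drifts.** Under equal means, with group shares p_i = n_i/N and k groups:

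- expected between-group mean square = Σ(1 − p_i)σ_i² / (k − 1)
- expected within-group mean square ≈ Σ p_i σ_i²

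A calibrated F test needs the ratio of these to be about 1.

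- Equal shares, k = 3: both equal Σσ_i²/3, so the ratio is 1 whatever the SDs.
- 60/25/15, smallest group SD × 1.5 (variance 2.25): (0.40 + 0.75 + 0.85 × 2.25)/2 = 1.531; 0.60 + 0.25 + 0.15 × 2.25 = 1.188; ratio 1.29.
- 60/25/15, smallest group SD × 2: (0.40 + 0.75 + 0.85 × 4)/2 = 2.275; 0.60 + 0.25 + 0.15 × 4 = 1.45; ratio 1.57.
- 70/20/10, largest group SD × 2: (0.30 × 4 + 0.80 + 0.90)/2 = 1.45; 0.70 × 4 + 0.20 + 0.10 = 3.10; ratio 0.47.
- 45/35/20, largest group SD × 1.5: (0.55 × 2.25 + 0.65 + 0.80)/2 = 1.344; 0.45 × 2.25 + 0.35 + 0.20 = 1.563; ratio 0.86. The distortion is milder when the split is milder.

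The total N cancels, so more patients do not help.

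**Step 2: simulated rejection rates, equal means, normal data, N = 1000.**

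| Sizes | More variable group | SD ratio | ANOVA | Welch |
|---|---|---|---|---|
| 450/350/200 | smallest | 1.25 | 6.5% | – |
| 450/350/200 | smallest | 1.5 | 8.4% | – |
| 600/250/150 | none | 1 | 5.1% | 5.1% |
| 600/250/150 | smallest | 1.25 | 7.1% | 4.8% |
| 600/250/150 | smallest | 1.5 | 9.7% | 4.8% |
| 600/250/150 | smallest | 2 | 15.5% | 5.0% |
| 700/200/100 | smallest | 1.5 | 12.4% | 5.3% |
| 700/200/100 | smallest | 2 | 19.7% | 5.4% |
| 700/200/100 | largest | 1.5 | 1.1% | 5.3% |
| 700/200/100 | largest | 2 | 0.3% | 4.7% |

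With 333 patients per group, ANOVA stays at about 5%.

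**Step 3: graded SDs, and whether N matters.** With a 60/25/15 split and SDs 1:1.25:1.5 and 1:1.5:2 (larger SD in smaller groups), ANOVA rejects 10.0% and 15.0% at N = 300, and 9.8% and 14.6% at N = 900. With the order reversed it rejects 2.1% and 1.5%, then 2.0% and 1.4%. Skewed gamma data (mean 6, sizes 180/75/45) give 14.8% with SDs 3:4.5:6 and 1.6% with SDs 6:4.5:3. Welch gives 6.7% and 4.9% there.

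**Step 4: power.** Sizes 700/200/100, both smaller groups shifted by 0.2 of their own SD, largest group more variable: at SD ratio 1.5, ANOVA 41% against Welch 58%; at ratio 2, about 18% against 44%. Sizes 180/75/45 with a 0.5 shift in the smallest group: with equal SDs, 79.3% against 78.5%; with SDs 2:1.5:1, 23.9% against 64.8%. With SDs 1:1.5:2, ANOVA rejects more often (54.0% against 28.8%), but in that setting it already rejects about 15% when the means are equal, so the excess is not usable power.

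**The case against.** The best reply is that this is detail for an analysis plan. The article says only 1-way ANOVA; Welch's test is itself a 1-way ANOVA, and R, the named software, runs both. This has weight: one phrase may settle the matter. But the article does name a test, the unqualified name conventionally means the pooled form, and nothing elsewhere points to the other.

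Second, both conditions for the problem are assumed. No passage shows that spread differs across groups, or that it lines up with size. That stands: the documents show only that neither is controlled. Under milder assumptions the error is small, for example 6.1% for two groups of 600 and 400 with the smaller one's SD 1.25 times as large.

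Third, the section on additional analyses promises adjusted analyses and sensitivity analyses that vary assumptions or methods. That wording could accommodate an unequal-variance check, but it names none and leaves the main test unchanged.

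Fourth, confounding by indication dominates any unadjusted comparison of approaches. This is true, and the fix does not touch it.

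A reader might also infer that the primary objective is compromised, because its example asks "How does individual center X compare to the national standard in terms of length of stay". The documents do not support that. Centers are to be set against national benchmarks built from risk-adjusted outcomes, which is a different analysis from an unadjusted F test across centers. Nor can one infer that the study will report false differences: the direction and size of any error are unknown until group sizes and SDs are seen.

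**Conclusion.** The point holds as a cheap improvement to a named method; it does not show that any result will be wrong. The ANOVA named here is miscalibrated when group size and spread both differ, and the design controls neither. On the assumed inputs, nominal 5% becomes about 6 to 16% when a smaller group is the more variable (SD ratio 1.25 to 2, splits from 45/35/20 to 60/25/15), and up to about 20% at 70/20/10. It becomes about 0.3 to 2%, with a substantial loss of power, when the largest group is clearly the more variable (SD ratio 1.5 to 2, splits of 60/25/15 to 70/20/10). It stays near 5% if sizes or SDs are about equal. Applying this to length of stay, cost and EQ-5D index, or to surgical approach, is a reading across sections, since the ANOVA sentence names neither outcomes nor groups.

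**What to change.** In the statistical methods section for primary and secondary outcomes, replace the ANOVA sentence with wording such as: *Differences across groups in continuous outcomes will be tested with Welch's 1-way ANOVA, which does not assume equal variances (in R, oneway.test with var.equal = FALSE). Linear regression coefficients will be reported with heteroscedasticity-consistent (HC3) standard errors.* The same sentence should say which groups and which continuous outcomes it covers.

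The cost is one sentence and a standard R option, with no extra data or patients. When variances are in fact equal the power loss is negligible (78.5% against 79.3% in the example above). Welch's test is itself approximate for small, strongly skewed groups (6.7% in the gamma example). The change corrects the error term only: confounding between nonrandomized groups still needs the adjusted analyses, and the benchmark comparison of centers needs its own risk-adjusted method.

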#### Secondary Objectives

The registry can be used simultaneously for multiple studies with different purposes. Among the secondary objectives are the following: (1) Economic impact assessment of innovative technologies or treatment pathways (eg, Do different surgical medical devices influence health care resource utilization for a single episode of hospitalization?) and (2) Psychosocial impact assessment of innovative technologies or treatment pathways, for example, minimally invasive surgery (eg, Do new targeted treatments have a beneficial or adverse impact on PROs?).

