### Participant Timeline

Recruitment will be conducted from January 01, 2024, to December 31, 2026. Follow-up will be performed for a minimum of 2 years. The study will be completed in the year 2028. The assessments at baseline and follow-up are presented in Table 1.

**Table 1 table1:** Study assessments.

Assessment	Baseline	Follow-up
Visit month (from inclusion)	Yes	No
Informed consent	Yes	No
Check if patient meets the inclusion/exclusion criteria	Yes	No
Medical history	Yes	No
Physical examination, including weight	Yes	No
Hematology	Yes	No
Blood chemistry	Yes	No
Radiological assessment	Yes	No
Clinical variables	No	Yes
Health-related quality of life	Yes	Yes
Direct and indirect costs	Yes	Yes

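### The only explicit test of group differences for primary and secondary outcomes is an unadjusted 1-way ANOVA, which can report baseline imbalance as effect in this nonrandomized comparison of surgical approaches

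*Protocol article*

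**What the plan says.** All references are to the protocol article.

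- **Statistical Methods for Primary and Secondary Outcomes.** Description comes first: "Descriptive statistics will be calculated for the whole sample and by relevant subgroups (age, gender, diagnosis, etc"). The next sentence is "Statistically significant differences across groups will be detected using 1-way ANOVA". Then: "Multiple linear regression will be performed to investigate the impact of participant characteristics on short- and medium-term outcomes". The following paragraph introduces the quality-of-life measure: "This study will use the official Italian EQ-5D-5L questionnaire to measure health and quality of life".
- **Participant Timeline, Table 1.** The row "Health-related quality of life" is marked for both baseline and follow-up, as is the row for direct and indirect costs.
- **Intervention Description.** "the choice of intervention will be based on factors such as tumor characteristics, patient condition", with the surgeon's expertise as a further factor. The allocation section confirms that the study is nonrandomized.
- **Explanation for the Choice of Comparators.** Comparing the outcomes of the surgical approaches is a stated aim.
- **Secondary Objectives.** The psychosocial objective gives minimally invasive surgery as an example of what is to be assessed, and asks: "Do new targeted treatments have a beneficial or adverse impact on PROs".
- **Primary Objectives.** National benchmarks are to rest on risk-adjusted outcomes.
- **Methods for Additional Analyses.** Adjusted analyses for confounders such as baseline characteristics and comorbidities are planned here, by regression and stratification.

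**The concern.** A 1-way ANOVA compares group means with no covariates. That is a weak basis for comparing groups that clinicians formed partly on patient condition. If patients who receive one approach start with a different quality of life, part of that difference persists at follow-up, and the test counts it as a difference between approaches.

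The information needed to do better is already scheduled, since EQ-5D-5L and costs are recorded at baseline. No section names them as covariates. The regression in the same section concerns participant characteristics and names neither surgical approach nor baseline EQ-5D-5L as a term. The confounder-adjusted analyses are placed among the additional ones, and nothing says whether they or the ANOVA carry the conclusion.

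At stake are the between-approach comparisons for psychosocial and economic outcomes, which could reflect who was selected for each approach. A lesser cost is precision, because the variance that baseline explains is left in the error term.

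**Working it through.** The article states no sample size, alpha, power, SD or correlation for this comparison, so there is no figure to reproduce. What follows illustrates the mechanism on assumed inputs.

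**Inputs, all assumed:** baseline imbalance between two groups δ = 0.3 SD; correlation between baseline and follow-up r = 0.4 to 0.7; n = 200 per group; equal SDs at both times; two-sided 5% test; no effect of approach given baseline.

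**1. Spurious difference in follow-up means.** Bias = r × δ.
- r = 0.4: 0.4 × 0.3 = 0.12 SD
- r = 0.7: 0.7 × 0.3 = 0.21 SD

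**2. Rejection rate with no effect.** SE = √(2/200) = 0.10 SD. Probability = Φ(bias/SE − 1.96) + Φ(−bias/SE − 1.96).
- r = 0.4: Φ(−0.76) + Φ(−3.16) = 0.224
- r = 0.7: Φ(0.14) + Φ(−4.06) = 0.556

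**3. Sensitivity to the assumptions.** The same formula with other inputs gives these two-group rejection rates:

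| δ (SD) | r | n = 100 | n = 300 | n = 500 |
|---|---|---|---|---|
| 0.1 | 0.3 | 5.5% | 6.6% | 7.6% |
| 0.3 | 0.3 | 9.8% | 19.7% | 29.6% |
| 0.3 | 0.5 | 18.6% | 45.1% | 66.0% |
| 0.3 | 0.7 | 31.8% | 73.0% | 91.3% |
| 0.5 | 0.7 | 69.7% | 99.0% | over 99% |

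The range runs from just above nominal to near certainty.

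**4. Three groups.** The article names three approaches, so a simulation used three groups of 200, baseline means shifted by 0, −0.15 and −0.30 SD, no true effect and 2,000 runs:

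| r | 1-way ANOVA rejects | Baseline-adjusted model rejects |
|---|---|---|
| 0.3 | 12.1% | 5.0% |
| 0.5 | 26.0% | 5.5% |
| 0.7 | 45.3% | 4.8% |

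Here all the imbalance runs through the baseline score, so adjustment removes it by construction. Real confounding by tumor characteristics or surgeon's expertise would not vanish this way.

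**5. Precision.** Adjusting for baseline multiplies the residual variance by 1 − r². The reduction is 0.4² = 16% to 0.7² = 49%. For an assumed difference of 0.25 SD at 80% power, the unadjusted comparison needs 252 per group; adjusted, it needs 229, 189 or 129 for r = 0.3, 0.5 or 0.7.

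**The case against.** The strongest reply is that the article does plan adjustment. Its primary objective depends on risk-adjusted outcomes, a multiple linear regression follows the ANOVA sentence directly, and a later section promises analyses that account for confounders. A reader might infer that ANOVA stands alone and that baseline imbalance will be reported as effect. The documents do not support that, because no section says the ANOVA carries the conclusion. What stands is that no section gives that role to the adjusted analysis either, and the only test named under the primary and secondary heading is the unadjusted one.

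Other tempting readings also go too far:

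- *That the ANOVA is expressly specified for EQ-5D-5L by surgical approach.* The sentence follows subgroups of age, gender and diagnosis, with an open-ended list, and EQ-5D-5L appears only in the next paragraph. The link is a fair inference from the section heading, not stated text.
- *That it is run on follow-up scores.* This is not stated. Change scores would not settle the matter: under the same assumptions the bias would be (r − 1) × δ, from −0.6 × 0.3 = −0.18 SD to −0.3 × 0.3 = −0.09 SD.
- *That fitter patients are steered to a particular approach, or that the same holds for targeted drugs.* The text on choice of intervention gives no direction and concerns surgery only. Baseline scores may differ; it does not say they will.
- *That the absence of a repeated-measures model is a defect in itself.* A journal article commonly leaves that to the full analysis plan.

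**Conclusion.** The concern holds in a limited form. For a nonrandomized comparison, the section on primary and secondary outcomes fixes an unadjusted test of group differences and leaves confounder-adjusted comparison to the additional analyses, at odds with the article's own risk-adjusted objective. Used for between-approach contrasts, that test can report baseline imbalance as effect and gives up precision that scheduled data would supply.

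The 0.12 to 0.21 SD and 22 to 56% figures depend wholly on the assumed imbalance, correlation and group size. The wider range in the working is the honest statement of uncertainty, and the size in LUCENT cannot be known from the article. No figure in the article is contradicted. This should be corrected before analysis.

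**What to change.** In the section on statistical methods for primary and secondary outcomes:

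1. State that the covariate-adjusted regression contrast is the main result for comparisons between surgical approaches. Covariates: the patient's baseline EQ-5D-5L (or baseline cost for cost outcomes), age, stage, comorbidity and centre.
2. Use a model suited to skewed data for costs.
3. Keep 1-way ANOVA only as a crude, descriptive comparison, labelled as such.
4. State that residual confounding may remain. Surgeon's expertise in particular is captured only in part by centre.

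The cost is a change of wording here and in any analysis plan, plus slightly more analysis work. Baseline quality of life, costs, medical history, tumor stage and demographics are already scheduled for collection. The adjusted model depends on complete baseline covariates; the multiple imputation already planned covers this.
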